## Abstract

**Background:**

Women in Bangladesh experience high rates of Intimate Partner Violence (IPV). IPV is more prevalent against income earning women compared to their non-earning counterparts, and Workplace Violence (WPV) is also common. Such violence is a violation of women’s rights, and also constrains them from contributing to their personal growth, household, community and the economy at large. There is limited evidence on what works to prevent IPV and WPV amongst garment workers. This paper describes an evaluation of HERrespect, an intervention which aims to reduce IPV and WPV against female garment workers in and around Dhaka, Bangladesh.

**Methods:**

The trial employs a quasi-experimental design, with four intervention and four control factories. In the intervention factories a randomly selected cohort of married female line workers, a cohort of male line workers, and all middle management staff received the intervention. The intervention strategies involved (1) gender transformative group-based training for workers and management staff; (2) joint session between workers (15 female and male) and middle-management staff; (3) factory-wide activities; (4) awareness raising among top management; (5) factory policy review and development and 6) a community based campaign. For the evaluation, a cohort of randomly selected female workers and a cohort of selected management staff have been established. All workers (*n* = 800) and management staff (*n* = 395) from these cohorts were interviewed at baseline using two different questionnaires, and will be interviewed in the endline, 24 months post-baseline. Intention to treat analysis will be used for assessing the impact of HERrespect, comparing the intervention and control factories.

**Discussion:**

To our knowledge this is the first study that seeks to evaluate the impact on IPV and WPV, of group sessions with female workers, male workers, and management; factory-wide campaigns and a community intervention among female garment workers in Bangladesh. Apart from informing programmers and policy makers about intervention effectiveness in reducing IPV and WPV against female garment workers this study will also present evidence on an intervention tailored to the situation in the garment sector, which makes HERrespect scalable.

**Trial registration:**

ClinicalTrials.gov NCT03304015, retrospectively registered on October 06, 2017.

**Electronic supplementary material:**

The online version of this article (10.1186/s12889-018-5442-5) contains supplementary material, which is available to authorized users.

## Background and rationale

Women in Bangladesh experience high rates of Intimate Partner Violence (IPV). In recent research, 54% of the ever-married women reported lifetime physical and/or sexual IPV and 27% of them reported exposure to this violence during the last 12 months [1]. Common correlates of IPV in Bangladesh include young age, poverty, low education, early marriage, witnessing abuse of mother by father in the family, childhood experience of violence, dowry, and poor spousal communication [2–5].

Gender inequalities shaping women’s experiences of IPV are widespread in Bangladesh. Women in Bangladesh are expected to be subservient, while men expect to control women and their sexuality. The social structure enforces this control by imposing confinement to home, *purdah*, restrictions on interactions with males and limits on employment. These norms constrain women’s social and financial power and skills, while positioning men in their “superior” role. Violence against women and girls (VAWG) is widely accepted and used as a tool for punishment of any transgression of social norms, for controlling women, and upholding men’s honour and status [6–8].

Despite the restrictions on women’s engagement in public spaces, more women are now involved in income generating activities. Women’s labour force participation rate is about 36% in Bangladesh [9], where 12% percent of the working women are employed in the manufacturing sector including garment sector. The ready-made garment (RMG) sector is the main driver of economic growth and formal employment in Bangladesh. In 2015, it contributed to 82% of Bangladesh’s total exports, valued at over $34 billion [10]. Over 4.2 million, usually low skilled, workers are formally employed in more than 4500 factories [11]. Similar to other labour intensive and export-oriented industries in developing economies, the RMG sector offers employment opportunities for women, particularly notable in a country where women traditionally do not work outside the home [12]. Approximately 80% of workers in the RMG sector in Bangladesh are women [13].

There are different perspectives on the impact of employment on women in the garment sector. For some young women in Bangladesh, it has contributed to their empowerment and changed their lives. Due to access to garment sector jobs, some young women delay marriage and childbirth [14]. And with their own income they are more likely to make their own decisions on spending that takes account of their health, leading to improvements in their well-being and that of their family [15]. Overall, formal employment and bringing home earnings may raise female workers’ value within their own family and may improve their capacity to negotiate within their households. They may see improvements in their position in the household vis-à-vis other family members [12, 14–16].

However, women’s employment may also increase their risk of abuse and physical violence. The literature on factors associated with IPV shows that in some patriarchal contexts, working women may be more vulnerable to IPV [3, 6, 8, 17]. According to the 2015 Bangladesh National Violence against Women Survey a higher proportion (33%) of income earning women reported physical and/or sexual violence during the past 12 months than their non-earning counterparts (26%) [1]. Some authors have suggested that employment may result in more violence if women are perceived to be challenging social norms and men’s provider role through their income-generating activities [18]. In addition, waged work may also increase conflict if women are tired after work and perceived as deficient in the domestic tasks that they are expected to carry out without male assistance, if men are suspicious about their wives meeting other men at work, suspicious when they come home late or intermittently work overtime, and if working and earning makes them challenge aspects of the gender regime at home.

Very little is known about workplace violence (WPV) against working women in low income settings. According to the Report on 2015 National Violence against Women Survey in Bangladesh women perceived the workplace as the second most likely place to experience violence after the household [1]. WPV against female workers in garment factories is also understudied. Scanty literature shows that despite the positive impact of formal employment in the garment sector on women’s economic and social empowerment, female workers are likely to experience violence in the factories. Fair Wear Foundation found that 75% of workers had experienced verbal violence at work, 20% experienced physical violence, and 30% had experienced psychological violence [13]. Sixty percent of female garment workers had experienced sexual harassment in the factories [13]. Qualitative research suggests that severe emotional and economic violence is common in this sector, while physical and sexual violence is not uncommon [19]. Most common perpetrators of workplace violence are mid- and low-level factory management staff, the majority of whom are male. The most common forms of violence facing female garment workers include name-calling, shouting, yelling, teasing, rough behaviour, being referred to using slang, and propositioning [20].

In general, evidence on what works in addressing IPV and WPV against working women, particularly garment workers is limited worldwide. Given the massive increase in women’s employment in factories globally, and specifically in Bangladesh, with the potential to increase women’s experiences of violence in the home and workplace, there remains a lack of effective interventions to reduce this. Although there is evidence that a combination of economic empowerment and gender interventions reduces IPV effectively in other settings [21–23] there has been no attempt at measuring the effect of gender interventions among female garment workers, who are relatively economically empowered compared to their peers. This paper describes an evaluation of HERrespect, an intervention which aims to address IPV and WPV against female garment workers in and around Dhaka. This research is being conducted by icddr,b in collaboration with South African Medical Research Council (SAMRC) and the intervention is being implemented by BSR, Change Associates Limited and WE CAN. The study is being conducted under the DFID-funded global programme “What Works To Prevent Violence Against Women and Girls?”

## Methods

### Objectives of the study

The primary objectives of the study are to assess whether the HERrespect intervention reduces female garment workers’ experiences of: (i) physical, sexual, and physical and/or sexual intimate partner violence and (ii) workplace violence in Bangladesh.

Additionally, the study will assess whether HERrespect is effective in: (1) increasing gender equitable attitudes, self-esteem, and knowledge and uptake of services for addressing IPV among female garment workers; (2) reducing acceptance of VAWG and the rate of depression among female garment workers; (3) increasing gender equitable attitudes and knowledge regarding laws and policies addressing gender discrimination and workplace violence against women among management; and (4) improving management styles and attitudes towards workers among management.

### Trial design

The trial employs a quasi-experimental design. It is being conducted in four intervention and four control factories. In the intervention factories a randomly selected cohort of married female line workers, a cohort of male line workers, and all middle management staff received the main intervention. In addition, factory-wide campaigns were carried out, and a community activity in one intervention community. For the evaluation, two cohorts have been established and will be followed up over 24 months in each of the intervention and control factories. One is a cohort of randomly selected female line workers (100 per factory) and the second is a cohort of selected management staff with frequent interaction with workers (50 in each factory). Two different questionnaires are administered for workers and management staff (see Additional files 1 and 2). All the workers and management staff from these cohorts were interviewed at baseline, and will be interviewed in the endline. The baseline was conducted before the intervention started, while the endline will be conducted 24 months post-baseline.

### The intervention

HERrespect is a workplace programme developed by BSR and SAMRC, with inputs from Change Associates Limited. Design of HERrespect is guided by the programmes Theory of Change and the formative research conducted by icddr,b.

#### Theory of change

The base of the Theory of Change begins with a core problem that female workers in the RMG industry in Bangladesh are susceptible to high levels of violence, both in the workplace and their intimate relationships. There is a lack of critical awareness about gender and rights among workers, and violence against women (VAW) is normalized and generally accepted in both workplace and intimate relationships. The dominant social norms in Bangladesh and the disciplinary nature of operating a factory reinforce the submissive identity of female workers and the unequal relationship between managers and workers. Female workers also have poor skills in communicating with managers and intimate partners and lack effective coping mechanisms to deal with stress. Moreover, workers do not have sufficient information on their rights and available resources at work and in the community.

To overcome the barriers, a combination of intervention strategies have been adopted to: (1) develop assertive communication skills; (2) build an understanding of gender and power and how it interplays in relationships; (4) reaffirm that violence is never justified; (5) acknowledge the stress facing female workers; (6) inform female workers of service providers and support within the factory, and (7) inform female workers of factory policies and local laws.

The goal of HERrespect is to cultivate more gender equitable attitudes and relationships among women and men in the RMG industry in Bangladesh, which ultimately will contribute to preventing VAW at workplace and intimate relationships. After participating in the interventions, workers are expected to become more willing and equipped to engage in respectful dialogue with managers/colleagues at work and intimate partners. They will have greater gender awareness and have less acceptance of the use of violence. It is expected that workers will have better coping mechanisms for stress. Finally, they should have greater awareness of prevention strategies and support services for abused women inside and outside the workplace. The theory of change is presented in Table 1.

**Table 1 Tab1:** HERrespect theory of change

Outcomes	Workers become more willing and equipped to engage in respectful dialogue with managers/colleagues at work and intimate partners	Greater gender awareness and sense of empowerment		Less acceptance and normalization of the use of violence	Workers have better coping mechanisms to work stress	Greater awareness on protection mechanism and support for abused women inside and outside the workplace	
Outputs	Workers are better able to communicate their needs at home and at work (i.e. asking for leave, explaining their needs, saying no in respectful ways)	Workers are more aware of how gender shapes their roles and responsibilities, and also how men can become more involved in care responsibilities.	Workers are more aware of how power affects their relationships and interactions with managers and their husbands	Workers can identify both joyful and harmful relationships, as well as ways to ameliorate them	Workers understand the sources of stress at work (collectively) and develop ways to deal with stress	Workers are aware of where to seek help inside and outside the factory	Workers aware of their rights and the responsibilities of the factory and the government
Exercises needed	Active listening; body language; attack, avoid, manipulate; I statements; saying no in respectful ways; assertive responses	Men and women: ideal and reality	Power over; statues of power	Joys and challenges; ways to get hurt; consequences of violence	Managing stress at work	Support systems for abused women; providing support as Change Makers	Factory policies and local laws
Inputs	Critical reflection on different ways of communicating (physical and verbal) through interactive activities	Understanding the impact of gender expectations (on both women and men) in their day-to-day lives	Reflecting on how power affects our relationships, how we communicate, how we make decisions	Sharing of experiences of violence at home, at work, in the communities, and its consequences	Sharing and mapping of the different points of stress at work	Explaining to workers the types of services (medical, legal, counseling, shelter) for abused women	Explaining to workers the factory policies and local laws
Responses	Develop assertive communication skills	Build an understanding of gender and how it impacts our roles and responsibilities	Build understanding of power and how it interplays in different relationships	Reaffirm that violence is never justified, no one deserves violence and everyone deserves respect in relationships	Acknowledge the stress facing female workers	Inform female workers of service providers and support within the factory	Inform female workers of factory policies and local laws
Barriers	Poor communication skills in speaking to managers/colleagues and intimate partners	Gender inequity plays out in the factory through male management dominance over female workers; at home, dominance of husbands over their wives		There is a general acceptance of the use of violence in relationships	Female workers are under constant stress and do not have proper coping mechanisms	Female workers have knowledge gaps - they are unaware of support services and their rights at work and outside of work	
Problem	Female workers are susceptible to violence both at work and at home. In the RMG setting, the use of violence is normalized, for instance, the use of name-calling and shouting. Female workers are at risk of sexual harassment. In Bangladesh, 73% of married women shared that they have experienced some form of violence by their partners in their lifetime.						

#### Intervention components

The HERrespect intervention consists of two components – a factory component and a community component. The factory component, which is the key focus of HERrespect was implemented by Change Associates Limited and the smaller community component was implemented by WE CAN. Better Work, an International Finance Corporation and International Labour Organization programme, provided technical advice on the development and review of factory’s violence and harassment policies. The intervention components in the workplace were:Separate gender transformative training for female and male workers (single sex groups) and management staff of 18 h (six 3-h modules), were held over 10 months and delivered to groups of 25 people, one module per month. The session topics include communication skills (e.g. listening, body language, etc.); assertive responses; reflection and discussion of gender roles and norms, and relationships; power; violence in relationships (causes, consequences and support system); stress and conflict management; factory policy analysis; goal setting and being a Change Maker. The curriculum is participatory, taking reference from Stepping Stones and Freirean reflective pedagogy.Joint sessions between selected workers (15 female and male) and middle-management staff (10), were held after the third, fifth and sixth group sessions.Factory-wide activities and campaigns using factories public address systems, skits and plays and other behaviour change communication materials.Awareness raising sessions among senior management (e.g., General Manager, Human Resources and Administration, Directors, etc), which were 2 h long.Factory policy review and development. Activities included at least one meeting every two months with the Factory Well-being Committee. The topics discussed included: reviewing existing and developing new gender policies and mechanisms to prevent and address sexual harassment; designing and implementing factory-wide promotional activities/campaigns; reporting on progress and challenges to senior management on a regular basis; and designing and implementing sustainability plans.

The small community engagement component, implemented by WE CAN, complemented the workplace initiatives by targeting the members of one intervention community where female workers of a selected intervention factory live. Specifically, the community component aims to mobilize men in the communities, including husbands of female workers and community elders and leaders, to prevent and combat VAWG at home and communities. Its activities included a video screening in the community, a couples’ fair, door to door campaign, meetings of Change Makers (including HERrespect participants) and a national sharing meeting.

### Study setting

The study is being conducted in Dhaka, Gazipur and Narayanganj districts in and around Dhaka, Bangladesh. Five study factories were selected from Gazipur district and one was selected from the Dhaka export processing zone situated outside Dhaka city. The remaining two factories are in Narayanganj, one of these is from a Bangladesh small and cottage industries corporation zone.

### Trial outcomes

Considering the objectives of the HERrespect intervention, four primary outcomes, split into two groups, were identified:Three primary outcomes are focused on: physical, sexual, and physical and/or sexual IPV experienced by female garment workers in the past 12 months:The proportion of women experiencing any physical IPV from husband during the past 12 months.The proportion of women experiencing any sexual IPV from husband during the past 12 months.The proportion of women experiencing severe physical and/or sexual IPV from husband during the past 12 months.

These outcomes are being measured using a set of questions based on the World Health Organization (WHO) violence against women instruments, which are designed to minimize reporting biases that arise from subjective perceptions of abuse by asking only about specific behaviours perpetrated by a male partner. The questions have been adapted for the “What Works To Prevent Violence against Women and Girls?” Global Programme and are being used across the evaluations within the programme.2.Violence witnessed or experienced at workplace in the past 4 weeks by female garment workers: This outcome is being assessed with an 8-item scale asked to the female garment workers, which was loosely developed as an adaptation of the peer victimisation scale [24]. The adaptation has been to measure ‘experiencing or witnessing’ victimisation as this was deemed to be less sensitive with factory management than actual reported victimisation. The adaptation of questions drew heavily on the findings of the formative research on the types of violence which occur in the work place.

The ten secondary outcomes are being assessed, reflecting hypothesised pathways of change leading to the primary outcomes. Four secondary outcomes focus on gender attitudes and responses to violence:Acceptance of VAWG amongst female garment workers: Acceptance of VAWG among female garment workers is being measured using statements adapted from the Gender Equitable Men (GEM) scale [25] and WHO multi-country study on women’s health and domestic violence against women [26].Gender equitable attitudes of management staff: Gender equitable attitude of the management staff is being measured using statements adapted from the GEM scale [25], WHO multi-country study on women’s health and domestic violence against women [26] and the South African study on men, masculinities, violence and HIV [27].Response to IPV amongst female garment workers: A single item explores women’s help seeking in response to IPV. The question heavily drew upon the WHO multi-country study questionnaire [26] and the SAFE questionnaire [28]. This question will only be asked to those who experienced physical and/or sexual violence during last 12 months.Knowledge of services in response to IPV amongst female garment workers: One question assesses the knowledge of the workers about where to seek help after experiencing IPV.

Two secondary measures assess women’s well-being:5.Self-esteem of female garment workers: The Rosenberg Self-Esteem scale is being used to measure self-esteem [29]. It measures global self-worth by measuring both positive and negative feelings about self. The scale is uni-dimensional and has shown strong convergent validity for men and women from different ethnic groups [30].6.Depression among female garment workers: Depression in the past week is being measured using the Center for Epidemiologic Studies Depression (CES-D) scale used widely in different settings (including Bangladesh) and showing high reliability and validity [31]. Each question is a statement and asked the respondent to answer how many days she has had particular feelings or ideas.

Four secondary outcomes focus specifically on management knowledge, practices and experiences:7.Management style: An adapted version of the social power scale developed by French and Raven (1959) and revised by Swasy (1979) is being asked to the female garment workers for measuring management styles of the managers [32, 33].8.Knowledge regarding laws and policies: The management staff are being asked five questions for assessing knowledge of the management staff on gender rights of women and protection of women against IPV and workplace violence guaranteed in laws and policies of Bangladesh.9.Attitudes regarding laws and policies: The management staff are being asked five questions to measure their attitudes regarding the existing laws and policies about protection of women against spousal violence and workplace violence.10.Burn out among management staff: The Maslach Burnout Inventory-Human Service Survey (MBI-HSS) is being adapted for measuring burnout of the management staff in the studied garment factories. The MBI-HSS has four subscales, which are Emotional Exhaustion (nine items); Personal Accomplishment (eight items); Depersonalization (five items); and three Optional items. Together, the subscales of the MBI-HSS provide a three dimensional perspective on burnout. Various studies regarding the MBI-HSS confirmed the soundness of the psychometric properties of the instrument (including variance of factor loadings), as well as its reliability and validity [34].

The summary of the trial outcomes is presented in Table 2.

**Table 2 Tab2:** Primary and secondary outcomes of the trial

	Typical Item	Response categories	Number of items	Cronbach Alpha for Worker data	Cronbach Alpha for Management data	Method of scaling	Hypothesis regarding expected change
Primary outcomes							
Physical IPV during past 12 months	In the past 12 months, how many times your current husband has slapped you or something to you that could hurt you?	Never, once, few, many	5	–	–	Binary - never compared to once or more	Decrease
Sexual IPV during past 12 months	In the past 12 months, how many times your current husband has physically forced you to have sexual intercourse when you did not want to?	Never, once, few, many	5	–	–	Binary - never compared to once or more	Decrease
Severe physical and/or sexual IPV during past 12 months	Questions asked for measuring physical and sexual violence during past 12 months	Never, once, few, many	10	–	–	Binary - never compared to once or more	Decrease
Witnessed or experienced workplace violence	In the past four weeks, how often have you experienced or witnessed a manager call a worker names?	Never, once, 2-3 times, many times	8	0.83		Mean	Decrease
Secondary outcomes							
Gender attitudes and responses to violence							
Acceptance of VAWG among female workers	In your opinion, does a man have good reason to hit his wife if she disobeys him?	4-point Likert: Strongly disagree, disagree, agree, strongly agree	6	0.69	–	Mean	Decrease
Positive gender attitudes among management staff	I think that a woman needs her husband’s permission to do paid work.	4-point Likert: Strongly disagree, disagree, agree, strongly agree	13	–	0.68	Mean	Decrease
Response to IPV	Did you go to any person/place for help when you experienced any physical or sexual violence during last 12 months?	Yes, no	1	–	–	Binary – yes compared to no	Increase
Knowledge of services in response to IPV	Do you know from where one can get help for such experience? If yes, where?	Yes, no	1	–	–	Binary – yes compared to no	Increase
Women’s well-being							
Self-esteem of the female garment workers	At times, You think you are no good at all.	4-point Likert: Strongly disagree, disagree, agree, strongly agree	10	0.76	–	Mean	Increase
Depression among female garment workers during past week	During the past week you thought your life had been a failure.	Rarely or none of the time; some or a little of the time; moderate amount of time; most or all of the time	13	0.87	–	Mean	Decrease
Management knowledge, practices and experiences							
Better management style of management staff	If you do not comply with your supervisor, you will not be rewarded	Very unlikely; Somewhat likely; Very likely	14	0.90	–	Mean	Increase
Correct knowledge regarding laws and policies	Are there laws/policies in this country that protect women from spousal violence?	Yes; no; don’t know	5	–	–	% correct compared to % incorrect	Increase
Positive attitudes regarding laws and policies	To your opinion - “Sexual remark and gesture is an act of workplace violence”	Strongly agree; agree; no opinion; disagree; strongly disagree	5	–		Mean	Increase
Burn out among management staff	You feel used up at the end of the workday	Never; A few times year; Monthly; A few times a month; Every Week; A few times a week; Everyday	16	–	0.67	Mean	Decrease

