### Sample size

For the worker survey, the sample size calculation was based on the primary outcome – physical IPV against female garment workers. Expecting 56% baseline prevalence of past year physical IPV experienced by the female garment workers (icddr,b unpublished data), and anticipating a 20% effect size, 5% level of significance and 80% power, the required sample size was 330 workers for both the intervention and control groups. To account for a 20% lost to follow up the sample size increased to 396 workers for both the groups, which was rounded up to 400. Thus, a sample of 100 workers would be required from each of the intervention and control factories, giving 800 in total.

For the management survey, the sample size calculation was based on gender inequitable attitudes among garment management staff. Anticipating 50% baseline prevalence of high or moderate gender equitable attitudes among the management staff, a 30% effect size, 5% level of significance and 80% power, the required sample size was 183 management staff for both intervention and control groups. Anticipating 10% loss to follow up, the sample size increased to 200 for both the groups. Thus a sample of 50 management staff would be required from each of the intervention and control factories, giving 400 in total.

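### The third primary outcome is labelled severe physical and/or sexual IPV, but Table 2 scores it as any physical and/or sexual IPV

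*Protocol article*

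**What the plan says.** All the relevant places are in the protocol article.

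- **Objectives of the study**, objective (i), names "physical, sexual, and physical and/or sexual intimate partner violence", with no severity qualifier.
- **Trial outcomes**, the lead-in to the list, also has no qualifier: "Three primary outcomes are focused on: physical, sexual, and physical and/or sexual IPV experienced by female garment workers in the past 12 months".
- **Trial outcomes**, the list itself, sets the first two outcomes as *any* physical and *any* sexual IPV. The third is "The proportion of women experiencing severe physical and/or sexual IPV from husband during the past 12 months".
- **Table 2**, third row, is labelled "Severe physical and/or sexual IPV during past 12 months". Its source items are given as "Questions asked for measuring physical and sexual violence during past 12 months", the number of items is 10, the response categories run from never through once and few to many, and the scaling is "Binary - never compared to once or more".
- **Table 2**, first two rows, gives physical IPV 5 items and sexual IPV 5 items, each with that same scaling. The typical physical item begins "In the past 12 months, how many times your current husband has slapped you".
- **Sample size** starts from physical IPV: "Expecting 56% baseline prevalence of past year physical IPV experienced by the female garment workers".

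**The concern.** A reader who sees *any*, *any* and then *severe* in one list expects the third outcome to be a narrower, more serious category than the other two combined. Table 2 contains nothing that narrows it: no subset of graver acts, no frequency cut-off, no count of acts. The cut-off is the one that defines *any* in the two rows above it.

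This is one of four primary outcomes. If the table is followed, the trial would report on severe violence when it had measured whether any violence occurred. That matters for a study meant to inform programmers and policy makers, because an effect on severe violence and an effect on any violence are different claims.

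**Working it through.** **1. Is the Table 2 score the same as any physical and/or sexual IPV?**

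Inputs from Table 2: 5 physical items, 5 sexual items, 10 items for the third outcome, and the same never versus once-or-more cut for all three.

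Reduce each item to never (0) or once or more (1).
- Physical IPV = 1 if at least one of the 5 physical items is 1.
- Sexual IPV = 1 if at least one of the 5 sexual items is 1.
- Third outcome = 1 if at least one of the 10 items is 1.

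There are 2^10 = 1,024 response patterns, and each set of 5 items has 2^5 − 1 = 31 non-zero patterns.
- Physical only: 31 × 1 = 31
- Sexual only: 1 × 31 = 31
- Both: 31 × 31 = 961
- Neither: 1

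The third outcome is positive in 31 + 31 + 961 = 1,023 patterns, which are exactly those in which the physical or the sexual outcome is positive. A direct enumeration of all 1,024 patterns found no exception. One slap, once, is enough to make the third outcome positive.

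**2. What prevalence does this imply?**

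P(third outcome) = P(physical or sexual) ≥ max{P(physical), P(sexual)} ≥ P(physical).

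With the planning value of 56% for physical IPV, the coded prevalence is at least 56%. The article gives no planning prevalence for sexual IPV, so no closer figure follows.

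**3. Is the sample size touched?**

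The article states 330 workers per arm for 56% prevalence, a 20% effect, 5% significance and 80% power. Read 20% as a relative reduction: p1 = 0.56, p2 = 0.8 × 0.56 = 0.448, difference d = 0.112, mean p = 0.504.

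n = [1.960 × √(2 × 0.504 × 0.496) + 0.842 × √(0.56 × 0.44 + 0.448 × 0.552)]² / 0.112² ≈ 312

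With the continuity correction, n' = (n/4) × [1 + √(1 + 4/(n × d))]² ≈ 330.

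The stated figure is reproduced (two-sided). It uses only physical IPV, so it does not depend on how the third outcome is defined.

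**4. Does the choice of definition matter for power?**

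The article gives neither a severity rule nor a prevalence of severe IPV, so only a range can be shown. The table takes 330 analysed per arm, a 20% relative reduction, two-sided 5%, no continuity correction and no clustering. Only the 56% is from the article; the other base rates are assumptions.

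| Base rate | Power |
|---|---|
| 10% | 14% |
| 20% | 27% |
| 30% | 41% |
| 40% | 57% |
| 56% | 82% |
| 65% | 93% |

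As coded, the outcome lies at 56% or above on the planning value. A genuine severity rule would put it somewhere at or below the any-IPV rate, possibly well below.

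**The case against.** **The label may be deliberate, and the objective merely broad.** A general objective followed by a more specific outcome is ordinary, and *severe* appears in both the list and the table. The 10 items do not rule out severity either, since a severity rule could be built from the same ten. This stands. The objective and lead-in alone do not prove an error. The conflict is between the label and the once-or-more cut-off, and the article does not settle which is the slip.

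**Severe might qualify only the physical part.** This does not rescue the row, because Table 2 admits all five physical items at once or more.

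**This is a condensed article.** A derivation rule may sit in a statistical analysis plan or with the questionnaire in the additional files. A reader might infer that the analyst is free to choose a definition after seeing the endline data. That is not shown, because an unseen plan may already fix it. The point does not need it: the article does not leave the scoring open, but states a rule that contradicts its own label.

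**A rate of 56% or more does not itself disprove severity.** A reader might infer that a severe outcome at least as frequent as any physical IPV is impossible. It is not. Severe physical and/or sexual IPV is a subset of the union of the two types, not of physical IPV, and the article gives no planning prevalence of sexual IPV to exclude it. The valid argument is the identity in step 1; the 56% is only a lower bound.

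**Conclusion.** The point holds as an internal inconsistency in the definition of a primary outcome. Under Table 2 as written, the outcome labelled severe is identical to any physical and/or sexual IPV, with a prevalence of at least 56% if the planning value for physical IPV is right. A reported effect on it would carry the wrong name.

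This rests on the plain reading of the Table 2 row, that once or more on any of the 10 items is positive. The article gives no other rule. The size of any mislabelling cannot be stated more closely, because the article has no figure for severe IPV. The sample size and the definitions of the other three primary outcomes are not affected. The definition should be corrected before endline analysis.

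**What to change.** Before endline data are analysed (the endline survey is planned for September to November 2018), make the label and the scoring rule agree, in one of two ways:

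1. Delete *severe* from the third item of the outcome list and from the Table 2 label. The outcome then matches objective (i), the lead-in and the existing scoring rule. This is the smaller change.
2. Keep *severe*, replace the once-or-more cut-off in that row with an explicit, pre-specified severity rule based on the responses already collected, and bring objective (i) and the lead-in into line. State that power for this outcome may be lower if it is rarer. The article offers no severity threshold, so the study team must supply and justify one.

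If a statistical analysis plan already holds a derivation, the article and that plan should be checked against each other and made the same. The cost is a few words in the outcome list and one Table 2 row, plus the objective under the second option. No new data are needed, because the frequency of each act is already asked.
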